## Abstract

**Background:**

It seems that nonspecific low back pain (NSLBP) cannot be successfully treated with a single intervention of any kind. However, a positive effect of an active lifestyle including physical activities in NSLBP is reported on pain and disability. Advising regular physical activity is one of the mainstays in physical therapy treatment, appealing to patients' adherence. Many patients with low back pain do not seem to adhere to their physiotherapist's advice. In this study, the influence of social support on adherence to an activity advice will be investigated.

**Objective:**

Objective of the study is to investigate if patients with low back pain randomised to receive social support adhere better to an activity advice than patients randomised to the control group.

**Methods:**

In a randomized controlled clinical trial, in private physiotherapy practices in the Netherlands, patients ≥18 years presenting with at least a second episode of nonspecific low back pain will be randomized over two groups: activity advice and social support as an add‐on to usual care versus usual care alone. The primary outcome measure is adherence to an activity advice measured by an activity monitor at 1, 6 and 12 weeks. All other objectives will be measured by questionnaires.

**Discussion:**

This project is the first comprehensive research project to assess whether social support influences adherence to an activity advice outside the clinical setting without supervision of a healthcare provider. Where evidence of influence on social support is lacking, findings may have implications for the management of patients with low back pain. In addition, findings may enable physiotherapists to predict in which patients with low back pain an activity advice with social support makes sense.

**ClinicalTrial.gov:**

NCT02996955.

## INTRODUCTION

1

It seems that nonspecific low back pain (NSLBP), particularly with a recurrent or persistent course, cannot be successfully treated with a single intervention of any kind (Friedly et al., 2010). A positive effect of an active lifestyle including physical activities is reported on pain and disability (Choi et al., 2010; Dahm et al., 2010; Hendrick et al., 2011; Ooijendijk, Wendel‐Vos & de Vries, 2007; Smith & Grimmer‐Somers, 2010; Staal et al., 2013; van Middelkoop et al., 2010; van Middelkoop et al., 2011; Wai et al., 2008). Therefore, advising an active lifestyle to patients seems logical, and optimal patient adherence to this advice is necessary to be successful in managing NSLBP. As clinical practitioners we experience patients' poor adherence to physical activity recommendations every day. This experience is supported by conclusions in literature that many sufferers do not seem to adhere to their physiotherapist's advice (Beinart et al., 2013; Kolt & McEvoy, 2003).

Poor treatment adherence in patients managed in physiotherapy outpatient settings is associated with low levels of physical activity, low self‐efficacy, perceived illness beliefs, depression, anxiety, helplessness, poor social support, long treatment duration, and increased pain levels during exercise (Jack et al., 2010; Medina‐Mirapeix, Escolar‐Reina, Gascón‐Cánovas, Montilla‐Herrador, & Collins, 2009; Medina‐Mirapeix, Escolar‐Reina, Gascón‐Cánovas, Montilla‐Herrador, Jimeno‐Serrano, & Collins, 2009). Besides, there is limited or conflicting evidence on the influence of clinical signs to adherence such as pain and disability, comorbidity, obesity, and number of episodes of health threat (Jack et al. 2010). To increase patient relevant outcomes as pain and disability, it is necessary to invent new, simple applicable treatment options to overcome the adherence issue. These options should influence reasons for suboptimal adherence.

Social support is known as one of the most important factors predicting physical health (Oraison & Kennedy, 2019). While various definitions of social support have been proposed in the literature, most research recognizes social support as the help perceived (i.e., emotional, practical) from others in social networks (Oraison & Kennedy, 2019). In this study, the influence of social support on adherence to an activity advice will be investigated. For the purpose of this study, it is hypothesized that organizing social support by a partner or friend will be a potential treatment option to increase adherence to a physical activity advice. This intervention fits the context of the new health definition where health is defined ‘as the ability to adapt and to self‐manage, in the face of social, physical, and emotional challenges’ (Huber, 2014).

There is evidence indicating that illness beliefs predict health behaviour and activity limitations in low back pain. To minimize negative influence of maladaptive illness beliefs on adherence to a physical activity advice in patients with low back pain (Siemonsma et al., 2013), in this randomized controlled trial, treatment of illness beliefs is added.

Because evidence on clinical barriers is conflicting and limited, influence of confounding factors, such as age, gender, education level, pain and disability, comorbidity, and patient's intention and attitude to physical activity will also be studied. It is hypothesised these factors influence adherence.

The primary objective of this study is to investigate if patients with low back pain randomised to receive social support adhere better to an activity advice than patients randomised to the control group.

Secondary objectives are; whether patients with low back pain perceiving social support during physiotherapy treatment adhere better to an activity advice compared to patients with low back pain without perceiving social support during treatment, and, if age, gender, education level, pain and disability, treatment of illness beliefs, comorbidity and attitude and intention to physical activity influences a patient's adherence to an activity advice.

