#### Baseline information

2.3.1

At baseline age, gender and education level will be registered.

To assess whether comorbidity influence adherence to an activity advice the medical burden of chronic illness is assessed with the Cumulative Illness Rating Scale (CIRS) (Appendix 1). The CIRS ranges from 0 (no illness) to 52 points and is a valid and reliable scale to measure comorbidities in clinical research (de Groot, Beckerman, Lankhorst & Bouter, 2003; Fortin et al., 2005).

It is hypothesised that overweighted/obese patients are protentional physical inactive. BMI of the patient will be calculated and categorized according to the WHO criteria (WHO, 2000).

It is hypothesised that the number of recurrences of low back pain influence adherence to an activity advice negatively, therefore, the number of recurrences of periods of low back pain will be noted.

To assess whether perceived pain and/or disability influences adherence to the activity advice, the visual analogue scale (VAS) for pain and the Quebec Back Pain Disability Scale (QBPDS) for disability will be used at baseline, both of which have been validated for assessing pain and disability (Bijur et al., 2001; Boer et al., 2004; Chapman et al., 2011; Smeets, Köke Lin, Ferreira & Demoulin, 2011) (Appendix 1).

Patients who refuse to enter the study will be asked to fill in the questionnaire at baseline (Appendix 1). The refusal questionnaire (RQ) is a study specified questionnaire collecting 13 reasons of refusal for entering the study (Barnes et al., 2012; Barratt et al., 2013; Williams et al., 2007).

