#### Secondary outcomes

2.3.3

The Social Support Scale is a study specific questionnaire and assesses the rate of social support perceived by the patient and performed by the partner (Appendix 1). This questionnaire must be filled in by the patient and the partner after the investigation period and has dichotomous outcomes.

The Dutch Illness Perceptions Questionnaire Short‐form (DIPQ‐S) assesses patients' and partner/friends' illness beliefs (Appendix 1). Eight items about illness beliefs are scored on a 0–10‐point scale, one item is an open question. The questionnaire has good reliability and validity (Broadbent et al., 2006; de Raaij, Schröder, Maissan, Pool & Wittink, 2012; Leysen et al., 2015). The DIPQ‐S will be filled in at baseline, 1, 6 and 12 weeks follow up by the patient and at baseline, 1 and 12 weeks follow up by the partner or friend.

The module attitude and intention (MAI) of The Knowledge, Attitude, Self‐efficacy and Self‐regulation, Exercise and Social Support for Sports and Exercise Questionnaire will be used to assess attitude and intention to be physically active (Wink, van Woerkom & Renes, 2006). Attitude (6 items) can be scored from 6 (most negative) to 42 points (most positive), while intention (3 items) can be scored from 3 (most negative) to 21 points (most positive). Validity of this questionnaire is unknown, but it was used in the FLASH! Campaign from the Dutch Institute for Sport and Exercise in 2003–2006 (Appendix 1). This questionnaire will be filled in at baseline and after 12 weeks by the patient and partner or friend.

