### Timeline

2.4

Eligible patients will be recruited for the study together with their partner or friend by the assessing physiotherapist and will receive information about the study. If patients and partners or friends decide after 1 week of consideration they want to be included in the study, written informed consent will be asked to the patient and partner or friend and base‐line assessment of the patient and partner or friend will be performed (Appendix 1). After base‐line assessment the assessor explains to the patient that further treatment will be performed by an IGP or CGP. The patient will be contacted within 2 days for an appointment with either the IGP or CGP. The patient and partner/friend will be instructed to come both to the next two appointments. The assessor contacts the randomization centre. The randomisation centre allocates the patient for IGP or CGP and informs the assessor. The assessor instructs the IGP or CGP to make the next appointments with the patient and their partner/friend.

After the first intervention on illness beliefs with or without organizing social support, treatment will be applied according to the Dutch guideline for low back pain (Staal et al., 2013). In both groups' patients are instructed in executing the activity advice in accordance with the DSHPA and to wear a move monitor for 1 week (Hildebrandt et al., 2007). In the group in which the social support is given, the partner/friend will be asked to make a week schedule of times, activities, and contact‐control moments for the coming months.

At the end of the week the activity monitors will be returned, and questionnaires will be filled out. The second intervention on illness beliefs with or without organizing social support takes place and treatment will be applied according to the Dutch guideline for low back pain (Staal et al., 2013). After six‐ and 12‐weeks patients will be invited by the assessors to wear the Active8 for one week and to fill in the questionnaires. During the study period the IGP contacts the partner/friend in week 6 and 10 to evaluate whether social support was given. At the last appointment also the partner or friend will be invited and asked to fill in questionnaires. Enrolment of the study is shown in the flow diagram (Figure 1).

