### Statistical methods

2.9

To analyse the data SPSS version 25.0 (IBM SPSS, Chicago, IL, USA) will be used. For demographic data descriptive statistics will be used and normality assumptions for the variables will be checked. An intention‐to‐treat analysis will be used for the main outcome. To correspond to the primary aim of the study, outcomes of the Activ8 will be dichotomized into adherent and not adherent patients in the intervention and control group. The Chi^2^ test will be used to investigate if there is a significant difference in the proportion of adherent patients to the activity advice between the intervention and control group after one, six and 12 weeks, and if there is a significant difference in the proportion of adherent patients between patients who experienced social support or not on the social support scale after 12 weeks. A Time Series Analysis will be used to present changes over time in perceived illness beliefs of patients and partner/friend. To understand whether illness beliefs influence adherence, Pearson's r between outcomes of the IPQ‐S at baseline and after 12 weeks and (non)adherence measured by the Active8, will be calculated, and linear regression will be used for modelling the relationship between these outcomes. To assess the correlation between attitude and intention to physical activity (MAI) and adherence at 12 weeks, Pearson's will be calculated, and linear regression will be used for modelling the relationship between these outcomes. Influence of age, gender, education level, comorbidity (CIRS), pain (VAS) and disability (QBPDS) on adherence, will be estimated by multiple regression analyses. A *p* value of <0.05 will be considered statistically significant.

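### The arm comparison is an unadjusted chi-square test although baseline factors expected to influence adherence are recorded before randomisation: a valid test, with some precision forgone

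*Protocol article*

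**What the plan says.** The Introduction of the protocol article lists factors to be examined alongside the main question, in a sentence that reads in part: "influence of confounding factors, such as age, gender, education level, pain and disability, comorbidity, and patient's intention and attitude to physical activity will also be". It then gives the expectation behind this: "It is hypothesised these factors influence adherence".

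Each factor has a baseline value:

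- Section 2.3.1: "At baseline age, gender and education level will be registered". Comorbidity (CIRS) is listed in the same section, as is pain on the VAS, and "the Quebec Back Pain Disability Scale (QBPDS) for disability will be used at baseline".
- Section 2.3.3, on the attitude and intention module (MAI): "This questionnaire will be filled in at baseline and after 12 weeks by the patient and partner or friend".

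Section 2.4 places allocation after the baseline assessment: "The assessor contacts the randomization centre. The randomisation centre allocates the patient for IGP or CGP and informs the assessor".

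Section 2.9 fixes the arm comparison: "The Chi^2^ test will be used to investigate if there is a significant difference in the proportion of adherent patients to the activity advice", applied at one, six and 12 weeks. The factors enter only separate correlation and regression analyses of what influences adherence, and no arm term is mentioned there. Section 2.7 stratifies randomisation on BMI and number of episodes, and these are also absent from the arm comparison.

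**The concern.** A baseline variable that predicts the outcome can be used in a randomised comparison to remove outcome variation unrelated to treatment. This gives a more precise estimate and corrects for chance differences between the arms. The protocol expects these factors to be predictive, collects them in time, and then compares the arms without them. Stratification helps balance BMI and number of episodes but does nothing for the other factors.

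What is at stake is precision in a trial planned for 142 evaluable patients. There is also a practical matter. Because the article itself calls these factors confounders, readers are likely to ask for an adjusted result. If the model is chosen after the data are seen, the choice of covariates is open to criticism.

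**Working it through.** **Inputs from the protocol article.** Section 2.5 gives 142 evaluable patients, 80% power and an unspecified medium effect at 12 weeks. Section 2.9 gives significance at p < 0.05. The allocation ratio is not printed. Two groups in blocks of four suggest 1:1, so 71 per arm is assumed.

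**The plan's own figure.** A two-by-two chi-square test with a medium effect (w = 0.3, 1 degree of freedom) needs 88 patients, so 142 is not reproduced. That is a separate matter and nothing below depends on it. At 142 patients, 80% power corresponds to w = 0.235.

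**Assumed adherence.** 30% versus 53% fits that power. The mean proportion is 0.415, so w = (0.53 − 0.30) / (2 × √(0.415 × 0.585)) = 0.115 / 0.493 = 0.233. The documents give no adherence rates, so this is an assumption.

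**Assumed prognostic strength.** This is expressed as s, the standard deviation of the covariates' joint contribution on the logit scale. The latent share explained is s² / (s² + 3.29):

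- s = 0.5: 0.25 / 3.54 = 7%
- s = 0.7: 0.49 / 3.78 = 13%
- s = 1.0: 1 / 4.29 = 23%

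**Power.** Simulation with 71 per arm, 30% versus 53%, four separately estimated normal covariates and 2,000 trials per row. The comparison is the chi-square test against the adjusted logistic test.

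| s | Chi-square | Adjusted | Gain (points) |
|---|---|---|---|
| 0 (irrelevant) | 81% | 81% | 0 |
| 0.5 (weak) | 79% | 80% | 1 |
| 0.7 | 80% | 84% | 4 |
| 1.0 (moderate) | 82% | 89% | 7 |

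The Monte Carlo standard error of each power is about √(0.8 × 0.2 / 2000) = 0.9 points, so single-point differences should not be over-read.

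A second simulation used two or eight covariates and control adherence of 20%, 30% or 40%. It gave gains of about 1 to 2 points at s = 0.5 and about 5 to 7 at s = 1.0. With irrelevant covariates the loss was at most about 1 point.

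**Variance of the risk difference, four covariates.** With irrelevant covariates it rises by about 2 to 3%. At s = 1.0 it falls by about 14%. With a slightly stronger set the ratio of adjusted to crude variance is 0.845, a fall of about 15%. In patients, 1 / 0.86 = 1.16 and 1 / 0.845 = 1.18, equivalent to roughly 16 to 18% more patients at the upper end.

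**Type I error.** Simulated values were 4.3 to 6.1% for the chi-square test and 5.1 to 5.6% for the four-covariate test. With eight covariates the adjusted test ran at about 5 to 7%, which is one reason to keep the set small.

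**Chance imbalance.** The arm difference in a standardised covariate has standard deviation √(2/71) = 0.168, so 95% limits are ±1.96 × 0.168 = ±0.33. At s = 1.0, an imbalance of 0.33 in the joint contribution moves the risk difference by roughly 0.33 × 0.30 × 0.70 = 0.07. That is 7 points, against the assumed difference of 23.

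**The case against.** The strongest reply is that nothing in section 2.9 is wrong. The primary objective is a difference in adherence between randomised groups, and a chi-square test of adherent proportions answers it directly with about 5% type I error. An unadjusted primary test is an accepted choice. This stands, and it limits the point to efficiency.

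The Introduction also describes the evidence on these factors as inconsistent and sparse, and makes their influence a secondary objective. Section 2.3.3 says that the validity of the attitude and intention module is not known. So the prognostic value may be weak and the gain close to nil. This stands too.

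The article is condensed, and an adjusted supporting analysis may exist in a fuller document. Its absence here is not criticised. The point concerns the test that section 2.9 does name for the primary aim.

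Three stronger readings are tempting, and the documents support none of them:

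- **That the comparison is confounded.** The article uses that word, but the arms are formed by concealed randomisation after the baseline assessment. The factors cannot bias the comparison systematically.
- **That the plan contradicts itself.** Expecting a factor to matter, and studying it separately, is compatible with an unadjusted primary test.
- **That chance imbalance is a second, likely harm.** With eight independent factors, the chance that at least one differs at p < 0.05 is 1 − 0.95⁸ = 34%. But pain and disability, or attitude and intention, are probably correlated, which lowers it. An imbalance matters only in proportion to prognostic strength, and the unadjusted standard error already allows for it. It largely restates the loss of power.

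**Conclusion.** The point holds as an optional efficiency improvement, not as an error. If the protocol's own hypothesis is right, the planned test is somewhat less precise than the collected data allow.

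The size rests on assumptions: 1:1 allocation, 71 evaluable patients per arm, 30% versus 53% adherence, and a prognostic strength that the documents do not give. Under these, four covariates add about 0 to 2 power points if weak and about 4 to 7 if moderate. Larger gains, about 9 to 11 points, need covariates explaining some 41% on the latent scale (s = 1.5), which is hard to defend given how the article describes the evidence. The downside is a variance about 2 to 3% higher if the four covariates turn out to be irrelevant. The conclusions of a trial analysed as planned would remain valid.

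**What to change.** In section 2.9, consider making the 12-week arm comparison, the time point used in section 2.5, a logistic regression of adherence on:

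- arm;
- the two randomisation strata, BMI and number of episodes, as used at randomisation;
- a small prespecified set of baseline covariates kept continuous, for example baseline MAI intention, QBPDS, VAS and CIRS. The 12-week MAI must not be used, because it is measured after randomisation.

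Report the standardised (marginal) difference in adherent proportions with a 95% confidence interval. A logistic coefficient alone gives a conditional odds ratio, whereas the standardised difference keeps the quantity that the chi-square test addresses. Fill isolated missing baseline values by mean imputation so that no randomised patient is dropped for a missing covariate. Keep the chi-square test as a supporting analysis.

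The number of terms should stay modest. At 30% versus 53%, about 71 × (0.30 + 0.53) = 59 patients are adherent, against seven terms in the model above. If adherence is expected to be much lower, fewer covariates should be named.

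The cost is analysis wording, fixed before the data are unblinded. No new data, visits or patients are needed.

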## METHODS

2

This study is a double blinded multicentre randomized controlled trial, with a concealed randomisation. This protocol was conducted according to Standard Protocol Items: Recommendations for Interventional Trials (SPIRIT) guidelines.

### Participants

2.1

The trial will be performed in 20 private practices for physiotherapy in the Netherlands. Dutch people have access to their physiotherapist without a referral of their GP. People with an additional insurance are compensated for the costs. For this study physical inactive patients with low back pain are needed. It is hypothesized that patients having more than one episode of NSLBP are potentially more inactive compared to patients with a first episode, therefore patients with a first episode of low back pain will be excluded. Patients ≥18 years presenting with a self‐reported second episode (or more) of NSLBP are recruited for the study. Eligible patients will be recruited for the study together with their partner or friend. Patients will be excluded for the study if (1) they cannot bring a partner or friend, (2) they are unable to read, write or speak the Dutch Language, (3) they present red flags as mentioned in the Dutch low back pain guideline (Staal et al., 2013) or, (4) when presenting with a medical history of cancer, osteoporosis, rheumatoid arthritis, tuberculosis, trauma and fractures in the lumbar spine as well as recent musculoskeletal system infections (Henschke et al., 2009; Staal et al., 2013). Only physically inactive NSLBP sufferers will be included, therefore, patients adhering to the Dutch Standard Healthy Physical Activity (DSHPA) which prescribes being moderately active for at least 150 min per week will be excluded as well (Hildebrandt, Bernaards & Stubbe, 2007).

Eligibility criteria for participating physiotherapists are: (1) being a certified graduate physiotherapist, (2) being instructed and updated on the content of the study.

During the first meeting all physiotherapists will be informed about the Dutch guideline for low back pain (Staal et al., 2013) and state of the art knowledge, to provide that treatment during the study will be in accordance with the guideline. Before the second meeting participating physiotherapists will be divided into three groups: in every clinic, an Assessor Physiotherapist (AP), an Intervention Group Physiotherapist (IGP) and a Control Group Physiotherapist (CGP) is needed. The second meeting will be for AP's, IGP's and CGP's separately. The AP's will be trained in knowledge about the study, inclusion criteria, exclusion criteria, informed consent, standardized intake forms and assessments. They will be trained how to communicate about the study in a positive manner to the patient and partner/friend. It will be explained to the physiotherapists how to adhere to the allocation procedure and how to register all investigational procedures and the use of the activity monitor. Participating CGP's will be instructed on the background and rationale of the study, treatment of illness beliefs, the activity advice, and the use of the activity monitor. Participating IGP's will be instructed on the same elements with an additional short course on how to motivate the patient and their partner/friend in organizing social support. Some participating physiotherapists are students Orthopaedic Manipulative Physical Therapy at the Rotterdam University of Applied Sciences, Rotterdam, The Netherlands. They participate in this study as APs where they must conduct a management assignment as part of their Master of Science educational program.

